## Abstract

**Introduction:**

Mild traumatic brain injury (mTBI) accounts for a significant proportion of emergency department (ED) visits, but current diagnostic protocols often lead to overuse of computed tomography (CT) imaging, despite low diagnostic yield. The BRAIN-CT trial evaluates the impact of rapid access to TBI biomarkers on decision-making for cranial imaging in patients with mTBI.

**Methods and analysis:**

This randomized controlled trial will enroll 350 adult patients aged 18–85 years presenting with suspected mild head injury (Glasgow Coma Scale 13–15) within 24 h of trauma. Participants will be randomized into two arms: (1) a biomarker-published group where ED providers receive real-time results of the i-STAT® TBI Cartridge test (detecting GFAP and UCH-L1), and (2) a biomarker-blinded group where results are withheld. The primary outcome is the proportion of patients undergoing CT imaging. Secondary outcomes include hospital length of stay, cost, neurological outcomes, and biomarker correlation with imaging findings. Analysis will involve chi-squared testing, logistic regression, and predictive modeling.

**Clinical trial registration:**

clinicaltrials.gov, identifier: NCT06932588.

## Introduction

Mild traumatic brain injury (mTBI) is the most prevalent form of head trauma presenting to emergency departments (EDs) globally, accounting for over 90% of the more than 5 million cases reported annually in the United States (1). About 82% of patients with mTBI undergo computed tomography (CT) imaging in the ED to exclude intracranial hemorrhage or other serious brain injuries, particularly in patients presenting with risk factors (1–3). However, this approach has led to the routine overuse of CT scans, with up to 90% of scans returning negative results and fewer than 1% of cases necessitating neurosurgical intervention (4–7). This overutilization contributes to increased healthcare costs, prolonged ED stays, and unnecessary radiation exposure (4–8).

The substantial economic burden associated with the acute evaluation of mTBI highlights the need for more efficient diagnostic pathways. In recent years, blood-based biomarkers have emerged as promising tools to improve triage decisions in patients with suspected mTBI. Several blood-based biomarkers have been studied in the context of mTBI including glial fibrillary acidic protein (GFAP), ubiquitin carboxy-terminal hydrolase L1 (UCH-L1), S100 calcium binding protein-B (S100B) among others (9–13). However, GFAP and UCH-L1 have both showed the highest sensitivity in predicting intracranial abnormalities on CT of the head in prospective observational cohorts (9, 12, 14). GFAP, an intermediate filament protein expressed by astrocytes, rises in the bloodstream over several hours following astroglial injury (15), whereas UCH-L1, a neuronal enzyme involved in protein turnover, increases more rapidly after neuronal damage (10). These complementary temporal profiles underpin the rationale for their combined use, which has demonstrated high sensitivity and negative predictive value (NPV) for detecting intracranial lesions in mTBI patients, with strong potential for ruling out significant intracranial pathology (9, 16). Table 1 summarizes the major clinical studies involving the utility of GFAP and UCH-L1 in mTBI.

**Table 1 tab1:** Clinical studies involving the utility of GFAP and UCH-L1 in mTBI.

Study	Sample size	Population	Age	Sample type	BM	Thresholds	Sens/Spec/NPV
Bazarian et al., 2018 (12)	1,920	Suspected mTBI (GCS 14–15)	≥18 years	Serum	GFAP, UCH-L1	GFAP: 22 pg./mL; UCH-L1: 327 pg./mL	Sens: 97.3%; Spec: 36.7%; NPV: 99.5%
Legramante et al., 2024 (13)	130	Suspected mTBI (GCS 13–15)	≥18 years	Serum	GFAP, UCH-L1	GFAP: 35 pg./mL; UCH-L1: 400 pg./mL	Sens: 100%; Spec: 27.6%; NPV: 100%
Papa et al., 2016 (14)	584	Trauma patients with and without mTBI	≥18 years	Serum	GFAP, UCH-L1	AUC for GFAP and UCH-L1	Diagnostic ranges of AUC were 0.80 to 0.97 for GFAP and 0.31 to 0.77 for UCH-L1 over 7 days.
Karamian et al., 2025 (15)	5,921	Suspected mTBI (GCS 13–15)	≥18 years	Serum/Plasma	GFAP, UCH-L1	GFAP: 4 pg./mL; UCH-L1: 64 pg./mL	GFAP: Sens: 98%, Spec: 15%, NPV: 97%; UCH-L1: Sens: 99%, Spec: 18%, NPV: 99%
Papa et al., 2012 (16)	96	Mild and moderate TBI	≥18 years	Serum	UCH-L1	UCH-L1: 0.09 ng/mL	Sens: 100%; Spec: 21%; NPV: 100%
Abbott i-STAT Whole Blood Test (17)	~250 (validation study)	Suspected mTBI (GCS 13–15)	≥18 years	Whole Blood	GFAP, UCH-L1	GFAP: 65 pg./mL; UCH-L1: 360 pg./mL	Sens: 96.5%; NPV: 96.5%

BM, biomarkers; mTBI, mild traumatic brain injury; GCS, Glasgow Coma Scale; Sens, sensitivity; Spec, specificity; NPV, negative predictive value.

The growing body of clinical evidence informed the development of the i-STAT TBI Plasma test (Abbott, Inc.), a point-of-care diagnostic tool that simultaneously measures GFAP and UCH-L1 concentrations. This test received FDA clearance (17) based on results from the ALERT-TBI study, which enrolled nearly 2,000 patients and demonstrated a sensitivity of 97.6% and an NPV of 99.6% for ruling out traumatic intracranial injury (9). Using the approved thresholds for both biomarkers, and despite high sensitivity for detecting intracranial injury, the specificity remains low (<40%) indicating that these tests are to be used to rule out intracranial pathology in mTBI rather than to rule in Table 1. Secondary analyses from ALERT-TBI further suggested that incorporating the i-STAT TBI test into ED workflows could reduce CT scan usage by approximately 40% (18). Both tested biomarkers where noted to be persistently elevated at least for 24 h after injury (19). Despite these promising findings, adoption of TBI biomarker testing in routine ED and trauma care remains limited, and integration into clinical algorithms is still evolving. Traditionally, TBI guidelines have routinely involved recommendations for CT head imaging for patients presenting with mTBI; however, emerging guidelines from Europe and recent recommendations from the NIH-NINDS TBI classification and nomenclature initiative have started to incorporate biochemical biomarkers in management of mild TBI (20–22).

The Biomarker Role in Assessing Imaging Needs for Mild Cranial Trauma (BRAIN-CT) trial is a prospective, randomized, double-blind clinical trial designed to evaluate the impact of real-time biomarker testing, combined with provider education, on CT utilization in patients with suspected mTBI. The study will employ the i-STAT Alinity instrument and i-STAT TBI Test (Abbott, Inc.), which provides quantitative measurement of the GFAP and UCH-L1 biomarkers in the whole blood samples at the bedside within 15 min, facilitating timely decision-making without impeding ED throughput. In addition to the primary outcome of CT scan reduction, the trial will assess secondary outcomes including the predictive value of biomarkers for intracranial pathology, length of ED stays, radiation exposure, hospital costs, and short-term functional outcomes.

This paper presents the rationale, design, and methodology of the BRAIN-CT trial and outlines the anticipated clinical implications of integrating blood-based biomarker testing into acute mTBI management.

## Methods and analysis

### Study objective

The BRAIN-CT trial investigates whether providing emergency-department clinicians with rapid GFAP and UCH-L1 results, via the point-of-care i-STAT TBI cartridge, changes imaging behavior in adults with mild traumatic brain injury. The primary objective (Table 2) is to compare the proportion of patients who receive a head CT scan between a biomarker-published arm and a standard-care (biomarker-blinded) arm; we hypothesize that real-time access to GFAP and UCH-L1 levels will lower the CT scan rate compared with standard management. To address this objective, we have designed a prospective, randomized, open-label, blinded-endpoint (PROBE) adaptive trial that will enroll 350 participants, randomized 1:1 to biomarker-published versus biomarker-blinded arms using permuted blocks stratified by age group, biological sex, race, and baseline Canadian CT Head Rule risk category (Supplementary Table 1). Frequent interim analyses with prespecified efficacy and futility boundaries will permit early stopping if criteria are met.

**Table 2 tab2:** Primary and secondary objectives of the BRAIN-CT trial.

Objective	Category	Objective description	Outcome measured
Primary	–	Evaluate whether real-time access to point-of-care TBI biomarker results (GFAP, UCH-L1) reduces the use of cranial CT imaging.	Proportion of patients undergoing head CT.
Secondary (clinical impact) two-arm comparisons	Clinical decision-making	Assess the impact of biomarker result access on physician decision-making for CT use.	CT imaging timing and provider rationale.
	Efficiency and cost	Determine whether biomarker use reduces ED/hospital length of stay and healthcare costs.	LOS, resource use, hospital charges. Perform a formal ICEA of biomarker testing versus standard care.
	Patient outcomes	Compare short-term outcomes between arms (neurological deterioration, readmissions, GOS, GCS).	GOS-E/GCS at 6 months and 1-year follow-up, neurological symptoms.
	Radiation exposure	Quantify radiation dose reduction per patient between arms.	Directly measure a key safety benefit.
	Disparity analysis	Identify patient subgroups (e.g., by age, injury mechanism, comorbidity) where biomarkers influence decision-making.	Stratified CT usage, subgroup analysis of impact.
	Safety monitoring	Monitor for adverse outcomes from missed injuries in biomarker-guided arm.	Adverse events, unexpected deterioration, delayed diagnoses.
	Time-to-imaging decision	Compare time from triage to CT decision between arms.	Evaluate whether biomarker access accelerates or delays decision-making.
	Disposition flow	Evaluate differences in ED-to-disposition pathways with vs. without biomarker data.	ED throughput times, floor/ICU admissions.
Secondary (validation) full cohort as single arm	Diagnostic accuracy	Determine sensitivity, specificity, NPV, and PPV of biomarkers vs. CT findings for intracranial lesions.	Biomarker levels vs. CT results.
	Kinetic profiling	Evaluate the kinetics and temporal profile of GFAP/UCH-L1 across 0, 8, 16, and 24 h.	Serial biomarker levels, time-to-peak and decay curves.
	Predictive modeling	Build multivariable models using biomarkers and clinical data to predict imaging-positive patients.	ROC curves, AUC, logistic regression outputs.
	Triage integration	Assess biomarker utility in supplementing current BIG criteria for TBI triage.	Sensitivity/specificity when combined with BIG criteria.
	Outcome prediction	Evaluate whether biomarker levels predict functional outcomes or neurologic decline.	Correlation with GOSE score, readmission, or symptom progression.
Secondary (implementation) only published cohort	Implementation feasibility	Assess provider adherence to biomarker interpretation guidelines in the biomarker-published arm.	Understand clinical adoption barriers and fidelity to protocol including provider and patient variables
	Patient perception	Evaluate patient understanding and satisfaction with biomarker-driven decision-making.	Gain insights into trust and acceptance of non-imaging diagnostics.

TBI, traumatic brain injury; CT, computed tomography; ED, emergency department; LOS, length of stay; ICEA, incremental cost-effectiveness analysis; GCS, Glasgow Coma Scale; GOS, Glasgow Outcome Scale; GOSE, Glasgow Outcome Scale-Extended; ICU, intensive care unit; NPV, Negative predictive value; PPV, Positive predictive value; ROC, Receiver Operating Characteristic; AUC, Area under the curve; BIG, Brain Injury Guidelines.

Secondary objectives are divided into three categories as summarized in Table 2; clinical impact, validation studies, and implementation studies. Clinical impact aims will explore whether access to biomarkers impacts the use of hospital resources, shortens length of stay, reduces radiation exposure, and predicts clinical outcomes. Validation objectives aim to replicate published data on the prognostic potential of the biomarkers studied on CT imaging and to study the timeline of biomarker changes in the blood after injury. Finally, implementation objectives study the predictors of incorporating guidelines into the decision making by providers.

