### Study design and methods

The BRAIN-CT trial is a single-center prospective, randomized, open-label, blinded endpoint study conducted in the ED of Grady Memorial Hospital, a level I trauma center. After completion of initial screening, 350 adults aged 18–85 years will be randomized 1:1 to either a biomarker-published arm (real-time GFAP and UCH-L1 values released to clinicians coupled to education on biomarker data) or a biomarker-blinded arm (standard care without biomarker disclosure). The study flow chart is provided in Figure 1. Allocation uses computer-generated permuted blocks stratified by age (3 Strata: 18–30, 31–50, 51–85 years), biological sex, race (2 Strata: Black, Not Black), Glascow Coma Scale (GCS) (2 Strata: 15, 13–14) and baseline Canadian CT Head Rule risk category (3 Strata: High Risk, Medium Risk, None) to balance key factors in routine decision making. The maximum sample size remains 350 participants for the initially planned cohort. Outcome adjudicators are masked to treatment assignments. Given the pre-existing FDA-approval of the use of the TBI biomarker testing in mild-TBI, the study is deemed no more than minimal risk to participants and a data safety and monitoring board was not required. This study is registered with clinicaltrials.gov (Identifier: NCT06932588), and the study was approved by the Institutional Review Board at Emory University and the Research Oversight Committee at Grady Memorial Hospital.

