### Primary efficacy analysis

The primary endpoint is the proportion of patients undergoing a head CT scan which will be reported as percentage of total patients. The key hypothesis:

H_0_ (null): There is no difference in CT head scan rates between the published biomarker and blinded biomarker arms.H_1_ (alternative): The published biomarker arm has a significantly lower CT scan rate compared to the blinded biomarker arm.

To evaluate the hypothesis, we will perform univariate analysis using a Pearson’s chi-square test followed by a pre-specified logistic regression model that adjusts for stratification/randomization variables (e.g., site, age, GCS score category), providing an adjusted odds ratio (aOR) and 95% confidence interval (CI). A statistically significant result will be defined with a two-tailed *p*-value of less than 0.05, or adjusted odds ratios for predicting CT head acquisition with a 95% confidence interval below 1.0. In the event the *p*-value approaches the significance threshold (e.g., p between 0.05 and 0.10), results will be interpreted with caution, and effect size estimates will be emphasized to assess the practical impact of the observed differences.

For subgroup analysis across randomization strata, we will use the same testing as primary hypothesis. Then, we will formally test for heterogeneity of treatment effect using interaction terms in the logistic regression models. A *p* < 0.05 for the interaction will be considered evidence of differential efficacy across subgroups (given the exploratory nature of interaction testing).

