### Sample size justification

Based on preliminary data from published studies, we defined a clinically significant impact to be attained at 15% reduction in the rate of CT head imaging in the published group, assuming 70% baseline CT utilization (23). Adjusting for an alpha of 5%, a total of 300 evaluable patients will be required (150/arm) to achieve at least 80% power to reject the null hypothesis. To account for patient withdrawal (change in exam before blood draw, leaving against medical advice, etc.), we will plan to target a maximum of 350 subjects enrolled.

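### The stated power of at least 80% is not the power of the announced design: 150 per arm gives about 77% with a single look, and nothing is allowed for the efficacy and futility looks

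*Protocol article*

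**What the plan says.** The Study objective section of the protocol article describes an adaptive design and says: "Frequent interim analyses with prespecified efficacy and futility boundaries will permit early stopping if criteria are met". Interim analyses come up again under Safety monitoring and under Rationale for randomization. The article gives no number of looks, timing, boundary shape or binding status.

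The Sample size justification plans for a "15% reduction in the rate of CT head imaging in the published group", "assuming 70% baseline CT utilization", and concludes that "a total of 300 evaluable patients will be required (150/arm) to achieve at least 80% power to reject the null hypothesis". Its only statement on error rate is "Adjusting for an alpha of 5"%. The rise to a maximum of 350 has one stated reason: "To account for patient withdrawal (change in exam before blood draw, leaving against medical advice, etc".). Interim looks do not appear in that section.

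Under Primary efficacy analysis the test is two-sided: "A statistically significant result will be defined with a two-tailed" p-value below 0.05. Under Study design and methods, "350 adults aged 18–85 years will be randomized 1:1", and 350 is repeated as the maximum.

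**The concern.** The sample-size section computes power for a trial analysed once. The Study objective section describes a trial that may stop at any of several looks. A futility look ends some trials that would have been significant had they continued, so with a fixed maximum and unchanged efficacy bounds the power falls. This loss is separate from the type I error question at the efficacy looks and remains when alpha is properly spent.

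If the single-look calculation had some slack, a mild rule might be absorbed. It has none, because the single-look figure is already below 80%. What is at stake is interpretation. A futility stop would be reported as no reduction in CT use and read against a stated power of 80%, while the chance of such a stop when the planned reduction is real is not given.

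**Working it through.** **Inputs.** Control rate 0.70, 15% reduction, alpha 5% and 150 per arm are from Sample size justification. The two-sided test is from Primary efficacy analysis, and 1:1 allocation from Study design and methods. The reduction is read as absolute, so 0.55 in the biomarker-published arm.

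**Step 1: the plan's own figure, one look.** The mean rate is (0.70 + 0.55)/2 = 0.625.

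- Standard error under the null: √(2 × 0.625 × 0.375 / 150) = 0.05590
- Standard error under the alternative: √((0.70 × 0.30 + 0.55 × 0.45) / 150) = 0.05523
- Power: Φ((0.15 − 1.960 × 0.05590) / 0.05523) = Φ(0.732) = **76.8%**

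The stated 80% is not reproduced. The unpooled and arcsine versions give 77.5% and 76.9%.

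**Step 2: size needed for 80%, one look.** n = (1.960 × √0.46875 + 0.8416 × √0.4575)² / 0.15² = (1.3419 + 0.5693)² / 0.0225 = 162.3, so **163 per arm** (326 in total).

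**Step 3: other readings.** A one-sided 5% test gives 85.3% at 150 per arm, but the primary analysis is two-sided. A relative reduction (70% to 59.5%) gives 47.7%.

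**Step 4: is there an allowance for looks?** 350 − 300 = 50, and 50/350 = 14.3%, all attributed to withdrawal. Nothing is set aside for the looks.

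**Step 5: what looks could cost (assumed rules).** The drift matching step 1 is θ = 1.960 + 0.732 = 2.692. I simulated B(t), Brownian motion with drift θ, at K equally spaced looks (the final one included), with Z = B/√t and 1,000,000 trials per number of looks. Efficacy is declared if Z ≥ C/√t, with O'Brien-Fleming constants C = 1.977, 2.004, 2.024 and 2.040 for K = 2 to 5. Futility rules apply at every interim and are always followed:

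- conditional power under the design effect: Φ((B + θ(1 − t) − C)/√(1 − t))
- conditional power under the current trend: Φ((B/t − C)/√(1 − t))
- effect in the wrong direction: Z < 0

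Power in %, with the probability of a futility stop under the planned effect in brackets:

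| Rule | 2 looks | 3 looks | 4 looks | 5 looks |
|---|---|---|---|---|
| Efficacy looks only | 76.6 | 76.2 | 75.9 | 75.6 |
| Design-effect conditional power <10% | 76.5 (1.1) | 76.0 (4.0) | 75.6 (6.7) | 75.2 (9.0) |
| Design-effect conditional power <20% | 76.2 (3.2) | 75.4 (7.7) | 74.7 (11.2) | 74.1 (13.9) |
| Z < 0 | 76.2 (2.8) | 74.4 (6.5) | 72.2 (10.1) | 70.0 (13.4) |
| Current-trend conditional power <10% | 73.0 (12.5) | 68.6 (20.9) | 64.8 (27.1) | 61.3 (32.1) |
| Current-trend conditional power <20% | 70.5 (17.6) | 64.7 (27.6) | 60.0 (34.5) | 56.0 (39.8) |

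The futility stops alone cost from 76.6 − 76.5 = 0.1 point to 75.6 − 56.0 = 19.6 points. Measured from the single-look 76.8%, the total loss runs from 0.3 to 20.8 points.

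**Step 6: if all 350 were evaluable (175 per arm).** The step 1 formula gives Φ((0.15 − 1.960 × 0.05175)/0.05113) = 82.9%. With 2 to 5 looks as in step 5, the design-effect rule at 10% leaves 82.6, 82.1, 81.9 and 81.6%. Z < 0 leaves 82.3, 80.5, 78.5 and 76.3%.

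**The case against.** The strongest reply is that the boundaries are called prespecified, so they may be set out in a full protocol or analysis plan that is not shown. An article may leave look times, boundary shapes and binding status to such a document. That stands, and their absence is no part of this point. It does not reconcile the two published statements: the article prints a power figure and a design, and the figure is not that of the design.

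A reader might infer that the futility looks must cost something like 5 to 20 points. The documents do not support that. Such a range fits Z < 0 or current-trend rules at several equally spaced looks. Rules based on conditional power under the design effect cost at most about 1.5 points in the table, and a non-binding rule that is overruled costs less. A reader might also infer that the looks should be cut back. That does not follow either: a futility rule trades power for earlier stopping, and that trade cannot be judged without the rule.

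A third reply is that 350 will be enrolled, and with all of them evaluable a mild rule stays above 80%. That is correct as arithmetic, but the plan assigns the extra 50 to withdrawal and makes its power claim at 300.

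Finally, the shortfall at a single look is not caused by futility stopping. About 3 points of any gap to 80% (80 − 76.8 = 3.2) belong to the fixed-sample calculation and should not be counted as a cost of the looks.

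**Conclusion.** The point holds in this form: the claimed 80% at 150 evaluable per arm is not met by the announced design. On an absolute reduction and the stated two-sided test, power is 76.8% before any interim look. No allowance is made for the looks, and futility stops that are followed can only reduce power further, given a fixed maximum and efficacy bounds that control alpha and are not relaxed to exploit the futility rule. The further loss cannot be determined from the article. Under the assumed rules the futility stops take from under 1 point to about 20 points, and the chance of stopping for futility when the planned reduction is real runs from about 1% to about 40%. Only the single-look shortfall is a firm number; the rest is an illustration of how much depends on a rule that the sample-size section does not take into account.

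**What to change.** In Sample size justification, replace the present claim with the power of the actual group-sequential rule at 300 evaluable patients. State the number and timing of looks, the efficacy and futility boundaries used in the calculation, and whether the futility rule is binding. Give the probability of a futility stop under the planned effect beside it, say that the reduction is absolute and the test two-sided, and make the section agree with Study objective.

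The cost is a short simulation or group-sequential calculation and revised wording. The stated power will be less favourable. Restating it needs no extra patients, but it also does not restore 80%; whether to accept the lower figure is for the sponsor to decide once it is known.

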### Secondary analyses

Relevant secondary analyses reported in Table 2 will be studies as described below:

Assess the impact of biomarker result access on physician decision-making for CT use (Time to obtaining CT head, *t*-test).Hospital Length of stay in published versus blinded group (*t*-test).Hospital costs for published versus blinded group (Incremental cost effectiveness analysis).GCS and GOS-E comparison in published versus blinded groups at 6 and 12 months (Ordinal logistic regressions).Compare rates of discharge, floor admission, and ICU admission between the published and blinded groups (logistic regression for each outcome, taking admission GCS and age as covariates).Within all patients, define the sensitivity and specificity for predicting GOS-E scores at 6 and 12 months for biomarker test as well as when combined with clinical variables and BIG criteria (ROC analysis).Within the published group, study predictors of adherence to biomarker-based guidelines among providers (logistic regression).

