### Expected impact of the proposed trial

We are currently unaware of Level I, evidence-based protocols that use blood biomarkers to guide cranial imaging after mTBI. The BRAIN-CT trial is designed to test whether a point-of-care GFAP and UCH-L1 assay, performed within 24 h of injury, can safely reduce CT utilization while maintaining clinical safety and lowering healthcare costs. Previous efforts to limit unnecessary imaging–such as the Canadian CT Head Rule–have demonstrated high sensitivity for detecting clinically significant injuries (2, 6), yet their clinical adoption has been inconsistent. Factors contributing to this include workflow variability, clinician preference, and perceived medico-legal risk (7). The BRAIN-CT trial addresses these limitations by offering an objective, rapid biochemical assessment that is integrated into routine ED workflows. Coupled with rigorous trial methodology, including randomization, blinded outcome adjudication, and cost-effectiveness analysis, BRAIN-CT is positioned to provide critical randomized data on the feasibility, safety, and clinical impact of biomarker-guided imaging decisions, helping to inform future multicenter studies and guideline development.

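### The monetary outcome is hospital charges in Table 2 but hospital costs in the analysis; if unconverted charges enter the cost-effectiveness analysis, the result is not a cost estimate

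*Protocol article*

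**What the plan says.** The protocol article refers to the economic outcome in four places.

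- **Study objective, Table 2, Efficiency and cost row, objective column:** "Determine whether biomarker use reduces ED/hospital length of stay and healthcare costs".
- **Same row, outcome column:** "LOS, resource use, hospital charges. Perform a formal ICEA of biomarker testing versus standard care". Charges are the only item in this list expressed in money.
- **Introduction, list of secondary outcomes:** "length of ED stays, radiation exposure, hospital costs, and short-term functional outcomes".
- **Secondary analyses:** "Hospital costs for published versus blinded group (Incremental cost effectiveness analysis".

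The section on expected impact adds that the trial is meant to test whether the assay "can safely reduce CT utilization while maintaining clinical safety and lowering healthcare costs". That is a statement of aim; no cost result is reported anywhere.

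**The concern.** A hospital charge is a billed price. A cost is the value of the resources consumed. The two differ by a mark-up, and nothing guarantees that the mark-up is the same for imaging, a laboratory cartridge, an ED stay and a ward or ICU bed. An analysis run on charges answers a question about billing. An analysis run on costs answers the question in the Table 2 objective.

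The article lists charges as what is measured and calls for the ICEA in the same table cell, yet elsewhere names costs as what is analysed. Someone building the dataset from Table 2 would extract charges. Someone following the Secondary analyses section would look for costs. At stake is whether a statement about healthcare costs at the end of the trial describes resource use or billing practice.

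**Working it through.** **Step 1. Figures in the article.** It gives no charge, unit cost, mark-up or cost-effectiveness ratio, so there is no stated figure to reproduce. The check below concerns direction only.

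**Step 2. The passages side by side.** The objective says costs, the Introduction says costs, and the named ICEA input is costs. The measured monetary item is charges. Charges and costs are not synonyms, so the outcome column disagrees with the other three places.

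**Step 3. What happens if charges are used without conversion.**

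Inputs:
- CTs avoided per patient: d = 0.15. This comes from the Sample size justification, "15% reduction in the rate of CT head imaging in the published group, assuming 70% baseline CT utilization", with the 15% read as an absolute difference.
- True cost of one CT: C = 100 units (assumed).
- True cost of one test: b units (assumed).
- Mark-up on CT, mC, and on the test, mB (assumed; both equal 1 when everything is valued at cost).
- Differences in length of stay are left out to keep the illustration simple.

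Formulas:
- Net saving per patient = d × C × mC − b × mB.
- Saving per avoided CT = net saving ÷ d. The article does not define this ratio; it serves here only as a scale.

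| Case | b | mC | mB | Net saving per patient at cost | Net saving per patient at charges | Per avoided CT, cost → charges |
|---|---|---|---|---|---|---|
| a | 5 | 3 | 3 | 15 − 5 = 10 | 45 − 15 = 30 | 66.7 → 200 |
| b | 15 | 3 | 3 | 15 − 15 = 0 | 45 − 45 = 0 | 0 → 0 |
| c | 20 | 3 | 3 | 15 − 20 = −5 | 45 − 60 = −15 | −33.3 → −100 |
| d | 10 | 3 | 5 | 15 − 10 = 5 | 45 − 50 = −5 | 33.3 → −33.3 |
| e | 5 | 2 | 4 | 15 − 5 = 10 | 30 − 20 = 10 | 66.7 → 66.7 |
| f | 20 | 3 | 1 | 15 − 20 = −5 | 45 − 20 = 25 | −33.3 → 166.7 |

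**Step 4. Reading the table.** With an equal mark-up m on both items, the net difference is multiplied by m and keeps its sign. A saving is enlarged (a), a null stays null (b), and a loss is enlarged (c). With unequal mark-ups the sign can change either way (d and f), or the errors can cancel (e). Case f values the CT at its charge and the test at its cost, a mixed basis that the article nowhere states.

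The direction therefore depends on relative mark-ups and on the true net difference, neither of which the article provides.

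**The case against.** The case against the point has three parts.

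1. **The article does not say that unconverted charges go into the ICEA.** In Table 2 the call for the analysis is a separate sentence after a list of three outcomes, and the Secondary analyses section already names costs as the input. This stands, and it is why the consequence is stated conditionally.
2. **Costs could be built without charges.** Resource use is in the same Table 2 list. The section on in-hospital assessment captures CT performance, ED and inpatient length of stay, and disposition. This also stands, and it makes the repair easy. It does not remove the conflict, because the article does not say that costs are to be built this way.
3. **A conversion may be set out in the full protocol or a health-economic plan.** Agreed: the absence of a conversion from a journal article is not counted here. What remains is that the article names its outcome in two incompatible ways.

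In the other direction, a reader might infer that the result will be inflated and the imaging saving overstated. With an assumed charge-to-cost ratio of 2 to 5, the imaging saving per patient would rise from 0.15 to between 0.30 and 0.75 times the cost of a CT. For some test prices a loss would then appear as a saving.

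One design feature lends this some plausibility. The cartridge is run in both arms, so a billed test would largely cancel from the difference in charges, and its price would have to be added separately. If it were added at purchase price while CTs were valued at charges, only the savings side would be marked up, as in case f.

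The documents do not support this as a finding. They give no mark-up and no basis for thinking imaging is marked up more than other services, and they do not describe that mixed valuation. Cases b to e show that the bias can also be nil or run the other way.

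**Conclusion.** The inconsistency is real: the measured monetary outcome in Table 2 is charges, while the objective, the Introduction and the named ICEA input are costs. If charges enter the ICEA unconverted, the incremental result is not a cost estimate and may be wrong in either direction. The size of the error cannot be obtained from the documents. The figures under the working rest on assumed unit costs and mark-ups and on the absolute reading of the 15% reduction; they show only that the direction is open.

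Neither a systematic overstatement of savings nor a cost conclusion already resting on charges can be claimed. The reference to lower healthcare costs in the expected-impact section is an aim. This is a secondary outcome, and the comparison of CT rates is unaffected. The point is worth acting on because the repair is small and the trial intends to report cost-effectiveness.

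**What to change.** In the outcome column of Table 2, replace hospital charges with hospital costs and state the source in one line. Any of these would serve:

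- the hospital's cost-accounting data;
- the resource use already collected, multiplied by unit costs;
- charges multiplied by department-specific cost-to-charge ratios, with imaging, ED, ward and ICU handled separately.

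Run the ICEA in the Secondary analyses section on that variable. Value CT, stay and the biomarker test on the same cost basis, and report charges descriptively only. If no costs can be derived, call it a charge analysis throughout and drop the cost wording from the objective and the Introduction.

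The price is a small text change and some extra costing work. The reported difference between arms may then move in either direction from what charges would have shown.
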